| **Full Study Title:** | Assessing the Role of Intraoperative Indocyanine Green Perfusion of the Transected Pancreas in Predicting Postoperative Pancreatic Leaks |
| --- | --- |
| **Protocol Number:** | IRB00025055 |
| **Investigational Product:** | indocyanine green |
| Version Number: | 1.1 |
| Version Date: | 10-17-23 |
| Replaces: | n/a |
| Principal Investigator: | [name], FACS, FSSO |
|  | Surgery  Oregon Health & Science University  [name]  [name]  [contact]  Fax: n/a  Email: [contact] |
| **Regulatory Sponsor:**  **(if different)** | **n/a** |
| **Statistician:** | [name] [name]  Biostatistics Shared Resource  [contact]  Fax:  Email: [contact] |

| # | **Section** | **Summary of Changes** | **Justification** |
| --- | --- | --- | --- |
| 1. |  |  |  |
| 2. |  |  |  |
| 3. |  |  |  |
| 4. |  |  |  |
| 5. |  |  |  |

| **Full Study Title** | Assessing the Role of Intraoperative Indocyanine Green Perfusion of the Transected Pancreas in Predicting Postoperative Pancreatic Leaks |
| --- | --- |
| **Protocol #** | IRB00025055 |
| **Coordinating Center** | OHSU, Knight Cancer Institute |
| **Clinical Phase** | other (specify) – Phase II Application of Approved Device and Drug |
|  | |
| **Study Description** | This study is designed to evaluate the association between intraoperative perfusion of the remnant pancreas and postoperative pancreatic fistula (leak) rates. Using an FDA approved drug (indocyanine green) and device (Stryker Spy Elite) for near-infrared imaging, we will assess perfusion of the remnant pancreas for patients undergoing pancreatectomy. We will then follow their postoperative course to evaluate whether a pancreatic leak developed, to determine if intraoperative perfusion correlates with leak rates. The aim of this study is to collect preliminary data on feasibility and association, with the ultimate goal of determining whether future investigation into modifying pancreatic perfusion will decrease rates of pancreatic leak. |
|  | |
| **Primary Objective** | Evaluate association between postoperative pancreatic fistula development and intraoperative pancreatic remnant perfusion. |
| **Secondary Objectives** | Evaluate the grade of leak via ISGPS classification and ICG metrics  Determine feasibility of intraoperative measurement of pancreatic perfusion using ICG and the SpyElite platform via a survey to be completed by OR staff.  Evaluate logistics of intraoperative perfusion measurement for staff and operating room using a survey. |
| **Primary Endpoint** | Incidence of biochemical leak or fistula after pancreatectomy defined by definitions of the ISGPS criteria |
|  | |
| **Key Inclusion Criteria** | Patients undergoing open pancreaticoduodenectomy or distal pancreatectomy for any diagnosis will be evaluated for inclusion. |
| **Key Exclusion Criteria** | Development of intra- or post-operative occurrences known to be associated with postoperative pancreatic fistula including hemorrhage, intraoperative blood transfusion, sustained postoperative hypotension requiring vasopressor support, unexpected ICU transfer, initiation of ACLS protocols will be excluded.  Patients with adverse reactions or allergies to indocyanine green will be excluded. History of prior pancreatectomy, prior severe pancreatitis, history of chronic pancreatitits, visceral vascular abnormalities, severe atherosclerosis, planned vascular reconstruction, hepatic insufficiency, liver fibrosis or cirrhosis will be excluded. |
| **Number of Participants** | *n* = 50 patients; anticipate screening *n =* 75 individuals. |
| **Duration of Therapy** | One 5.0 mg IV dose of indocyanine green, intraoperatively, with repeat intraoperative dosing up to maximum 2mg/kg |
| **Duration of Follow Up** | Thirty (30) days. |
|  | |
| **Description of Study Intervention** | Study participants will undergo one intraoperative measurement of pancreatic remnant perfusion. This involves intravenous administration of indocyanine green dye during their operation followed by immediate near-infrared perfusion measurement using the Stryker SpyElite camera, targeted at the organ of interest prior to drug administration. The intervention is expected to take five minutes total. |
|  | |
| **Statistical Analyses** | Chi-square test will be used to evaluate the association between leaks and perfusion. Logistic regression analysis will be further utilized to evaluate covariates influencing the presence/absence of leaks, with specific attention to the predictive value of percent maximum perfusion metrics and time to maximum metrics at the set timepoints in the protocol. With leaks of any severity occurring in a minimum 20% of pancreatectomies based on extensive published data. Our projected sample size of 50 will achieve 80% power to detect at least 25% difference in leaks rate between two group assuming 20% leak rate for normal ICG perfusion group.  We plan to enroll patients on a rolling basis. With a liberal estimated exclusion of 30% due to the multiple and complex postoperative factors known to be associated with leak (hemorrhage, sustained hypotension, vasopressor requirements included in “Exclusion Criteria”) we anticipate screening 75 patients and enrolling 50. The overall study will be paused if the following events occur: Life-threatening grade 4 toxicity attributable to protocol therapy that is unmanageable, or unexpected, death suspected to be related to ICG injection, as indicated by statistical stopping rules in this protocol. |

SCHEMATIC OF STUDY DESIGN

[figure not shown]

|  | **Preop visit** | **Surgery and Postoperative Period** | | | | |
| --- | --- | --- | --- | --- | --- | --- |
| **Procedure** |  | **Day 1 (Day of Surgery)** | **Day 4±3**  **(Post-operative Day 3)** | **Day of Discharge** | **Discharge + 7-14 Days (Post-Operative Follow-up)** | **Day 30** |
| Physical exam | x | X | X | X | X |  |
| Vital signs^1^ | x | X | X | X | X |  |
| ECG (if indicated) | x | X |  |  |  |  |
| Routine blood draw^2^  (1 tablespoon) |  | X | X |  |  |  |
| Drain Fluid Analysis for amylase |  |  | X |  |  |  |
| Pregnancy test (if indicated) | x | X |  |  |  |  |
| Review any adverse events |  | X |  |  | X | X |
| Review all other medications |  | X |  |  |  |  |
| ICG |  | X |  |  |  |  |
| Pancreas Resection |  | X |  |  |  |  |

TABLE OF CONTENTS

[TABLE OF CONTENTS 7](#_Toc1924134513)

[LIST OF TABLES 7](#_Toc453567276)

[LIST OF FIGURES 7](#_Toc1478094859)

[LIST OF ABBREVIATIONS 7](#_Toc1089401493)

[0. BACKGROUND INFORMATION AND SCIENTIFIC RATIONALE 9](#_Toc2112760570)

[0.0 Background 9](#_Toc1747993032)

[0.0.0 Overview of study disease(s) 9](#_Toc2072564894)

[0.0.1 Overview study intervention(s) 10](#_Toc2069882099)

**No table of figures entries found.**

LIST OF ABBREVIATIONS

| AE | Adverse event |
| --- | --- |
| ALP | Alkaline phosphatase |
| ALT | Alanine aminotransferase |
| ANC | Absolute neutrophil count |
| AST | Aspartate aminotransferase |
| ATC | Anatomical Therapeutic Chemical (Classification System) |
| AUC | Area under the curve |
| BMA, BMB | Bone marrow aspiration/biopsy |
| BUN | Blood urea nitrogen |
| CBC | Complete blood cell (count) |
| CFR | United States Code of Federal Regulations |
| CoC | National Institutes of Health (NIH) Certificate of Confidentiality |
| CR | Complete response |
| CRC | Clinical Research Coordinator |
| CRMS | Clinical research management system |
| CRQA | Clinical Research Quality & Administration |
| CRRC | Clinical Research Review Committee (OHSU) |
| CRF | Case report form |
| CSF | Cerebral spinal fluid |
| CT | Computerized tomography |
| CTCAE | Common Terminology Criteria for Adverse Events |
| CTEP | Cancer Therapy Evaluation Program |
| CTMS | Clinical Trial Management System |
| DFS | Disease-free survival |
| DLT | Dose limiting toxicity |
| DP | Distal Pancreatectomy (cf. RAMPS) |
| DSMB | Data and Safety Monitoring Board |
| DSMC | Data and Safety Monitoring Committee |
| DSMP | Data and Safety Monitoring Plan |
| ECG, EKG | Electrocardiogram |
| ECOG | Eastern Cooperative Oncology Group |
| eCRF | Electronic Case Report Form |
| eCRIS | Electronic Clinical Research Information System |
| EDC | Electronic data capture |
| FCBP | Female of childbearing potential |
| FDA | United States Food and Drug Administration |
| GCP | Good Clinical Practice |
| HBeAg | Hepatitis B “e” antigen |
| HBV | Hepatitis B virus |
| HCT | Hematocrit |
| HCV | Hepatitis C virus |
| HGB | Hemoglobin |
| HIPPA | Health Insurance Portability and Accountability Act |
| HIV | Human immunodeficiency virus |
| IB | Investigator’s Brochure |
| ICF | Informed Consent Form |
| ICG | Indocyanine Green |
| ICH | International Conference on Harmonization |
| IDE | Investigational Device Exemption |
| IEC | Independent Ethics Committee |
| IND | Investigational new drug application |
| IP | Investigational product |
| IRB | Institutional Review Board |
| iwCLL | International Workshop on Chronic Lymphocytic Leukemia |
| IV | Intravenous |
| LDH | Lactate dehydrogenase |
| LFT | Liver function test |
| MedDRA | Medical Dictionary for Regulatory Activities |
| MRI | Magnetic resonance imaging |
| MTD | Maximum tolerated dose |
| MUGA | Multiple Gated Acquisition |
| N/A | Not applicable |
| NCI | National Cancer Institute |
| NHL | Non-Hodgkin’s lymphoma |
| OHRP | Office for Human Research Protections |
| OHSU | Oregon Health & Science University |
| ORR | Overall response rate |
| PD | Pancreaticoduodenoectomy (aka: Whipple Procedure) |
| PDAc | Pancreatic Ductal Adenocarcinoma (aka: Pancreatic Cancer) |
| PET | Positron emission tomography |
| PI | Principal Investigator |
| PK | Pharmacokinetics |
| PO | *Per os* (by mouth, orally) |
| POPF | Post-Operative Pancreatic Fistula (aka: “leak” or “fistula”) |
| PR | Partial response |
| QOL | Quality of Life |
| RAMPS | Radical anterograde modular pancreaticosplenectomy (Radical distal pancreatectomy) |
| RBC | Red blood cell (count) |
| RP2D | Recommended Phase II Dose |
| RNI | Reportable new information |
| RT | Radiation therapy |
| SAE | Serious adverse event |
| SD | Stable disease |
| SD | Standard deviation |
| SGOT | Serum glutamic oxaloacetic transaminase |
| SGPT | Serum glutamic pyruvic transaminase |
| TSMP | Trial Specific Monitoring Plan |
| UA | Urinalysis |
| ULN | Upper limit of normal |
| UP | Unanticipated problem |
| VAPORHCS | Veteran Affairs (VA) Portland Health Care System |
| WBC | White blood cell (count) |

# BACKGROUND INFORMATION AND SCIENTIFIC RATIONALE

## Background

[figure not shown]

Cancer of the pancreas will cause more than 50,000 deaths this 2023 in the US alone. The incidence of pancreatic cancer has been growing by 1% a year for the last two decades.^1^Pancreatic cancer has one of the lowest overall 5-year survival rates of all organ tumors, with 5-year-survival rates estimated at around 10%. 5-year survival rates can increase to more than 30% when tumor and patient characteristics allow for resection.^2^ Open pancreaticoduodenectomy and distal pancreatectomy are the treatment of choice when tumors are limited to the pancreas. These surgical procedures have high rates of morbidity, with the most serious complication being pancreatic leaks. It is estimated that up to 30% of all patients that undergo removal of the pancreas develop a pancreatic leak. Typically, undetectable at time of surgery, pancreatic leaks occur at the pancreas to bowel anastomosis (fig 1a, yellow arrow). Diagnosis is done when clinical suspicion is high and entails measurement and analysis of suction drains (fig 1b). Pancreatic leaks prolong postoperative hospital length of stay, delay initiation of chemotherapy and increase risk for infection.^3^ Because adequate recovery is hindered by pancreatic leaks, minimizing the risk for this complication is of uttermost importance for improving patient outcomes. Recent studies have analyzed different methods to predict the risk for developing a pancreatic leak after pancreatectomy with variable success. However, these methods involve postoperative measurements. ^4, 5^ Because it arises from dual embryologic sources, the surgical neck of the pancreas is a poorly perfused watershed region of the gland, subject to hypoperfusion.^6, 7^ Ischemia of the pancreatic remnant is a factor for the development of leaks.^8-10^ Currently, surgeons rely on direct visualization of pancreatic tissue and ultrasound to estimate optimal blood flow. Present methods have been of limiting value in predicting adequate blood flow in both open pancreaticoduodenectomy and distal pancreatectomy.^11-12^ An improved intraoperative technique to analyze blood perfusion could guide surgical margins to minimize risk for pancreatic leaks. Indocyanine green (ICG) fluorescence is a method widely used to assess blood perfusion of tissues during surgery. ICG use is described in recent literature of pancreatectomy.^13-15^ However, there is no prospective systematic analysis of its use in assessing the risk of developing a pancreatic leak.

Figure 1. A) Reconstructed Whipple with typical leak site Image by Cancer Research UK / Wikimedia Commons; B) Closed suction drain. Public Domain Image. Images from Wikimedia Commons under Creative Commons Attribution (CC BY) 4.0 license.

- - 1. Overview of study disease(s)

**Pancreatic tumors**:

90% of all tumors of the pancreas are of the ductal adenocarcinoma type. With more uncommon tumors including neuroendocrine tumors, among others. While there are no clear-cut causes in most cases, patient risk factors include tobacco and alcohol use Genetic mutations with BRCA and ATM are considered known genetic patterns that increase risk for pancreatic adenocarcinoma. Up to half of all adenocarcinomas of the pancreas present symptoms once they are in a metastatic stage. Only about 1 in 5 patients are diagnosed in an early enough stage of disease where it is considered resectable by surgery.^16^

- - 1. Overview study intervention(s)

While the study is designed to examine the utility of near-infrared imaging and post-transection perfusion of the remnant pancreas on the prevalence of pancreatic leaks, ***the intervention planned is solely the addition of ICG administration and intraoperative near-infrared imaging***. Standard-of-care surgeries as planned by the attending physician are described below (“Distal pancreatectomy” and “Open pancreaticoduodenectomy”) **but are not considered study interventions.**

**Distal pancreatectomy**:

Encompasses the removal of the last part of the pancreas and sometimes removing the spleen. This procedure is indicated when a lesion is located in the tail of the pancreas. Some patients with chronic pancreatitis may also have indications for a distal pancreatectomy. However, most of these procedures are performed for tumor removal. Distal pancreatectomy has an overall mortality rate of 3% and morbidity of 47%. Most common serious adverse effect is pancreatic leak/fistula, and it occurs in around 30% of patients that undergo distal pancreatectomy.^17^

**Open pancreaticoduodenectomy**:

Also called Whipple procedure, entails the removal of the head of the pancreas, duodenum, a part of the stomach and the gallbladder. Surgical techniques have improved mortality rates of this procedure and large-scale studies estimate a mortality of 4%.^18^

**Indocyanine green**: is an FDA-approved dye which emits light when near-infrared light is applied to it. ICG can be injected intravenously or directly to certain tissues. When applied intravenously, ICG travels to tissues by arteries. During surgery, near-infrared light can be used to visualize an overlay of ICG over the normal image of the tissue. ICG then delimits the tissue exemplifying blood perfusion in that area. ICG use was first described more than 50 years ago. Notably, with a 1958 study describing its uptake and excretion in liver and biliary tracts.^19^ Since then, studies of ICG both in the lab and in clinical trials, have shown promising results of its use in different surgical procedures. Yearly published studies on PubMed for ICG have more than doubled from 2012 to 2022, with 651 and 1519 studies respectively. ICG has demonstrated an excellent safety profile in clinical trials among different gastrointestinal surgeries, including recently in pancreatic surgery.^20^

**ICG in surgery of the pancreas**:

ICG has been extensively used in surgical fields, including but not limited to colorectal, hepatic and gynecological surgery. However, pancreas surgery studies on ICG have been more limited. Recent studies on ICG use in pancreatectomies have been promising for this evolving field. There is one case-report of a single patient where hypoperfusion was seen with ICG after pancreatectomy and then developed a fistula.^21^ Consensus surveys show pancreas surgeons have a favorable outlook to ICG in procedures because it does not prolong surgical time and its great safety profile on patients. A cohort of pancreas surgeons recently expressed their interest in further studies regarding better visualization of tissue blood perfusion using ICG.^22^

**ICG for evaluation of leaks after pancreatectomy**:

To date, there has been only one study directly regarding the use of ICG for pancreatic leak after removal of the pancreas. However, their hypothesis was done retrospectively in only one patient after the surgery.^21^

## Study Rationale

Current methods of evaluation for poor tissue perfusion are not ideal. Surgeons rely on visualization of the pancreatic remnant and assessment of the color and texture of the pancreas. Recently use of ultrasound has aided as another measure for tissue perfusion. However, ultrasound is operator-dependent by nature and does not provide an objective parameter. Studies show poor correlation of visual data surgeon gathers and actual tissue perfusion.

Our hypothesis is that remnant pancreas perfusion will be easily and objectively evaluated with intravenous ICG followed by imaging.

- - 1. Known Potential Risks

An immediate risk that would be presented to patients with ICG administration is exposure to an agent that could cause an adverse reaction even if there is no previous personal history of it. Overall adverse reaction to systemic ICG is estimated to be around 5% with only 0.05% as serious adverse reactions.^23, 24^ The most common adverse reactions include nausea, extravasation of ICG and urticaria. As per FDA drug insert, anaphylaxis has been reported with use of ICG. Less than 10 confirmed cases of anaphylaxis by ICG under general anesthesia are available in current literature.^25^ Addition of ICG to a surgical procedure seems to add neglible risk for adverse effects to the baseline risk of the surgery itself.

- - 1. Known Potential Benefits

Potential benefits include the possibility of detecting low perfusion tissue during surgery

Long range potential benefits: if ICG uptake correlates with pancreatic remnant perfusion, critical information for avoiding hypoperfusion will be available for clinical decisions. This study aims to investigate the relationship between hypoperfusion in surgery and postoperative leak development. Currently, no measurable, modifiable intraoperative intervention is known to decrease leak rates. Our long-range goal is carrying forward a positive outcome from this study into a clinical trial evaluating improving remnant gland perfusion and whether this may decrease postoperative fistulae.

# OBJECTIVES AND ENDPOINTS

## Primary Objective and Endpoint

| **Primary Objective** | **Endpoint** | **Start** | **End** |
| --- | --- | --- | --- |
| To determine if altered measurement results of ICG after pancreatectomy is associated with leak rates. | Incidence of biochemical leak or fistula after pancreatectomy defined by definitions of the ISGPS criteria | Day of surgery | Measurement of drain fluid amylase in postoperative period up until day 30 |
|  | Perfusion status measured by ICG metrics | Day of surgery | Day of surgery |

## Secondary Objectives and Endpoints

| **Secondary Objective** | **Endpoint** | **Start** | **End** |
| --- | --- | --- | --- |
| To evaluate the grade of leak via ISGPS classification and ICG metrics | Leak grade via ISGPS classification | When a leak is detected | Last day of postoperative follow-up (day 30 after surgery) |
|  | ICG metrics | Day of surgery | Day of surgery |
| Determine best practices of usage of ICG for pancreatic surgery | Results of short verbal survey to surgeon and other OR members | During the first 15 measurements. | At surgery number 15 |

# STUDY DESIGN

## Description of the Study Design

*Refer to* Section 11*, Statistical Analysis for additional information regarding statistical methods used in this study.*

This is a Phase II study to assess diagnostic parameters of hypoperfused pancreatic cut edge via ICG and its relation to fistula formation versus conventional measurements. The study design consists of a single arm intervention group (n=50).

The trial will commence with the enrollment of the fifteen patients, after these 15 casesa logistics run-in of the OR ICG technique and timing will be done. During the logistics run-in, the PI will evaluate team satisfaction and measurement outcomes. This will be done through the application of a 3-question paper-based quality survey, attached in the supporting documents for the protocol. If an average score below 50% is given, study will be terminated to avoid negative impact on the logistics of pancreatectomies. Survey scores are calculated depending on the answer given, A= 0% B = 16.5% C = 33%. Minimum score 0 maximum score 100. Progressive study enrollment will continue throughout the adjustments, and enrollment will be halted if any major concerns arise. If the interim analysis does not result in study termination, enrollment of the remaining participants will resume to enroll a total of 50 patients completing study intervention and follow-up.

Aside from interim analysis evaluating logistics. A patient safety analysis will be performed at the same time. Herein, potential factors of the clinical trial that could negatively impact patient outcomes will be addressed. These factors include adverse effects of ICG administration and factors from the clinical trial process that negatively impact the conventional treatment course of patients. If any concerns are identified on interim safety analysis, the study could temporarily pause enrollment until the issues are addressed. This is to supplement study stopping rules delineated in 9.6 and Data and Safety forms.

The study schedule will be divided into 2 periods: (1) the intra-surgical period which starts at the time of ICG injection and ends when the surgical procedure is terminated and (2) the postoperative period which begins at the end of surgery and ends 30 days postoperatively.

We will use a cutoff of 60% of the maximum ICG uptake to consider cut edge as poorly perfused. (100% measured 4-6 cm from the cut edge of the pancreas point 5 and 6 in the figure below). Additionally, to compare with non-pathologic gastrointestinal tissue perfusion, ICG uptake metrics will be captured from the gastric body.

[figure not shown]

At the completion of the proposed study, the expected outcomes are to have evaluated the safety and efficacy of intra-operative ICG administration in the assessment of pancreatic perfusion at the cut edge.

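### The run-in survey's item points, its stated maximum of 100 and the 50% termination threshold do not reconcile: the points sum to at most 99, and a midpoint form scores 49.5

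*Protocol*

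**What the plan says.** Everything that matters here stands in one paragraph of the Protocol, Description of the Study Design. The instrument is a "3-question paper-based quality survey, attached in the supporting documents for the protocol". The item points and the range are given together: "Survey scores are calculated depending on the answer given, A= 0% B = 16.5% C = 33%. Minimum score 0 maximum score 100". The consequence is mandatory and the inequality strict: "If an average score below 50% is given, study will be terminated to avoid negative impact on the logistics of pancreatectomies".

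No other section changes the points, gives a rounding or rescaling rule, or says what happens at exactly 50. The table in Secondary Objectives and Endpoints places the survey "During the first 15 measurements" and describes it as "Results of short verbal survey to surgeon and other OR members", so the mode (verbal or on paper) also differs between the two sections. Neither section gives the number of respondents per case. The survey form is a supporting document that is not shown.

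**The concern.** The points look like thirds of 100 that were rounded down, with the stated range and the threshold left on the unrounded scale. Rounding of that kind would not matter in a descriptive summary. Here the score feeds a rule that ends the trial, and the rounding falls exactly at the threshold. Two analysts with the same forms could reach opposite decisions, one by adding the points as printed and the other by taking a percentage of the maximum. If that came to light only after the forms had been collected, the choice between the two readings would be made with the answer already known.

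**Working it through.** **Inputs**, all from the Protocol, Description of the Study Design: 3 questions; A = 0, B = 16.5, C = 33; stated range 0 to 100; terminate if the average is below 50.

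**1. Stated range.** Minimum: 3 x 0 = 0, which agrees. Maximum: 3 x 33 = 99, which does not agree with 100. The attainable totals are 0, 16.5, 33, 49.5, 66, 82.5 and 99.

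**2. Midpoint.** All B: 3 x 16.5 = 49.5. One each of A, B and C: 0 + 16.5 + 33 = 49.5. Both are below 50. As a share of the attainable maximum, 49.5/99 = 50.0%, which is not below 50.

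**3. Answer patterns.** Of the 27 possible patterns on one form, 17 score below 50 with the printed points. With exact thirds (0, 50/3, 100/3) the number is 10. The seven that change side are all B and the six orderings of A, B, C.

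**4. Averaging per question instead of summing.** The score would then be at most 33 and the study would always terminate, so this cannot be what is meant.

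**5. Width of the affected band.** Let d be the mean number of C answers minus A answers per form. The average over forms is 16.5 x (3 + d). Continuing requires 16.5 x (3 + d) >= 50, so d >= 50/16.5 - 3 = 0.0303 per form. Divided over three answers this is 0.0303/3 = 1.01% of all answers. With exact thirds the requirement is d >= 0. The two scorings therefore disagree only for d from 0 to just under 0.0303, that is, for averages from 49.5 to just under 50 on the printed points.

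**6. What that means for a finite number of forms.** The Protocol does not give the number, so these are assumptions. Count A, B, C as 0, 1, 2, so that each form has 6 steps.

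| Forms | Total steps at which the decisions differ | Average on printed points |
|---|---|---|
| 15 | 45 | 49.5 |
| 33 | 99 | 49.5 |
| 45 | 135, 136 | 49.50, 49.87 |
| 75 | 225, 226, 227 | 49.50, 49.72, 49.94 |

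Up to 33 forms, only an average at exactly the midpoint is affected.

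**7. How often the rounding would change the decision.** The answer mixes are assumed, and answers are treated as independent.

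| A / B / C | 15 forms | 45 forms | 75 forms |
|---|---|---|---|
| 10 / 50 / 40% | 0.08% | about 0 | about 0 |
| 20 / 40 / 40% | 1.6% | 0.1% | 0.01% |
| one third each | 7% | 8% | 10% |
| 0 / 98 / 2% | 40% | 25% | 17% |

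The last row sits almost on the boundary and shows the extreme. In the one-third row, exact thirds would themselves terminate the study about 46 to 48% of the time.

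**The case against.** The best defence is that the paragraph shows its own intent. A third of 100 rounded to 33, beside a stated maximum of 100 and a threshold given as a percentage, suggests that 99 was simply treated as full marks. On that reading a midpoint average is 50% and the study continues. This is plausible, and it is why one cannot say that the text fixes the wrong decision. It does not remove the defect, because the paragraph prints points and a maximum that disagree and leaves the reader to choose between them.

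A second objection is that the matter is small: half a point, in a logistics survey, with no bearing on the primary endpoint, the chi-square test, the sample size or the separate safety review. This stands, and it sets the severity.

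A reader might go further and infer that a neutral team verdict is certain to end the study. The document does not support that. B is the middle score, but the form is not shown, so its meaning is unknown. Nor does the document say that a middling verdict ought to let the study continue, since the purpose given for the rule is to protect operating-room logistics. A reader might also take the 40% in the last row above as the typical risk. That figure depends on an assumed mix of answers with no A at all and on an assumed 15 forms.

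**Conclusion.** The concern holds as a minor error that is wrong as written. The item points, the stated maximum and the threshold cannot all be correct: the maximum is 1 point short and the midpoint 0.5 point short. The termination decision depends on the reading only when the average lies from 49.5 to just under 50. Outside that band the error is harmless.

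The mismatch itself needs no assumption. The size of the band assumes that a form's score is the sum of its three items and that the average is taken over forms. Any probability of a changed decision also needs the number of forms and the mix of answers, which the Protocol does not give.

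**What to change.** In Description of the Study Design, and on the survey form, score each item 0, 1 or 2 and report each form as total/6 x 100, with no rounding before averaging. The scale then runs from 0 to 100 and a midpoint form scores 3/6 x 100 = 50 exactly. Do not print decimal item points instead: 16.67 and 33.33 would give a maximum of 99.99 and an all-B score of 50.01.

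Keep termination for an average below 50, and add that an average of exactly 50 continues, as the strict inequality already implies. In the same edit, align the survey mode between the two sections.

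The cost is a line or two in the Protocol and a revised form. Participants, endpoints and sample size are not affected. The change should be made before the run-in survey is scored, so that the rule is not interpreted after the answers are known.
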